## Study Outcomes and Data Analysis

### Efficacy Outcomes

As we expect a short, 5-day course of tDCS to have a short-lasting effect on brain function, we will only assess short-term outcomes at 28 days after the end of tDCS.

The primary efficacy outcome will be the change in headache days from the 28-day baseline to the 28-day follow-up period.

The secondary outcomes will include the change in migraine days, headache hours, mean pain intensity (0–10 Visual Analog Scale), acute treatment consumption (doses), migraine-related disability (mMIDAS score) and impact (HIT-6 score), quality of life (SF-36 score), sleep quality (PSQI score), and anxious and depressive symptoms (HADS score) from the 28-day baseline to the 28-day follow-up period. The change in the number of days with low, medium, and high disability will also be assessed by using of a specifically designed headache diary (Supplementary Material 2).

The additional outcome will be the changes in spectral power and coherence in the delta (1–4 Hz), theta (5–7 Hz), alpha (8–12 Hz), and beta bands (13–30 Hz), both overall and over the occipital regions, at EEG recording between the two measurements (before vs. after tDCS). The EEG power changes will be correlated with the improvement in primary and secondary outcomes. The age limit of 40–70 years was chosen to limit the variability in EEG activity generated by the inclusion of too young or old subjects, which could act as a confounder in outcome assessment.

Each outcome will be assessed in the group of active and sham tDCS; additionally, between-group comparisons will be made.

A migraine day will be defined as a day with headache lasting at least 4 h if left untreated and accompanied by typical symptoms (nausea, vomiting, photo- and/or phonophobia) or preceded by aura. All days with headache not accompanied by any of those symptoms will be considered as non-migraine headache days. The total count of headache days will include both migraine and non-migraine headache days.

### Safety Outcomes

Safety assessment will include adverse event reporting. Adverse event monitoring will be performed during the tDCS stimulation sessions and during the 28-day follow-up period after tDCS. Adverse events will be detected and collected by investigators with a standard questionnaire (35) and open-ended questions. Monitoring for serious adverse events (SAEs) will be performed according to common clinical practice.

### Statistical Analysis

Continuous data will be summarized by mean, standard deviation (SD), median, first and third quartiles, minimum and maximum, Categorical data will be presented by absolute and relative frequencies (n and %). Bilateral 95% confidence limit will be presented as appropriate.

Comparison between groups (active/sham) for the variables under study (headache days, days of disabling headache, intensity of pain, consumption of acute treatments, headache-related disability, and scores on questionnaires) will be performed using parametric or non-parametric statistics, depending on the data distribution.

Primary analyses will be performed on primary and secondary outcomes. Exploratory subgroup analyses will be performed on patients with a history of menstrual migraine and on patients with chronic migraine with medication overuse.

To evaluate electrophysiological changes, the dependent variable will be the variations in EEG activity after vs. before tDCS. Specifically, we will compute the spectral power *via* Fast Fourier Transform (FFT) and the coherence in cortical activity among brain areas via magnitude-squared coherence (MSC) for the artifact-free epochs in each EEG frequency band. For each group of patients (tDCS vs. sham), the power change before vs. after tDCS will be compared for each electrode and each frequency band. Given the results of a previous study (36), particular attention will be given to power in the alpha band in occipital areas. The EEG index changes will be correlated with changes in migraine parameters (headache days, migraine days, pain intensity, acute medication consumption, questionnaires score) to directly link the modifications in brain physiology to the frequency and severity of migraine episodes. Source current density of cortical generators of relevant EEG indexes will be also assessed by low-resolution electromagnetic tomography (LORETA) (37), to confirm the cortical origin of the physiological changes induced by tDCS. Outcomes will be compared between the active and sham tDCS groups by chi-squared or t-test statistics as appropriate.

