## Inclusion and Exclusion Criteria

Our trial will follow the guidelines issued by the International Headache Society for neuromodulation in headaches (30). The protocol follows the SPIRIT checklist (31, 32) (Supplementary Material 1). The inclusion criteria will be the following:

- male or female patients, aged between 40 and 70 years, referring to the Headache Center of the University of L'Aquila;- a diagnosis of migraine with or without aura according to the International Classification of Headache Disorders, 3rd Edition (33);- migraine must have been present for at least 12 months;- treated with CGRP-MAbs (erenumab, fremanezumab or galcanezumab) for 90–180 days since the first subcutaneous administration (this time range was chosen to ensure a stable CGRP pathway inhibition);- reporting ≥8 monthly migraine days in the last 30 days of observation despite treatment with CGRP-MAbs;- able to discriminate between migraine and tension-type headaches;- written informed consent to participate in the study.

Treatment with CGRP-MAbs will be prescribed according to Italian reimbursement criteria, i.e., in patients reporting ≥8 monthly migraine days with a Migraine Impact and Disability Assessment Scale score ≥11 and having failed at least three preventive medication classes among beta-blockers, tricyclic antidepressants, anticonvulsants, and onabotulinumtoxinA.

Patients with other concomitant primary headache types will be included if attacks are <1 day/month and <12 days/year.

Subjects with medication overuse headache and menstrually-related migraine will be not excluded from the study but will be included in exploratory subgroup analyses. According to the clinical practice of the recruiting center, patients with medication overuse will not undergo detoxication treatments.

The exclusion criteria will be the following:

- use of any concurrent migraine preventive medication other than CGRP-MAbs;- secondary migraine-like headache;- epilepsy or any other neurologic condition that may be worsened by transcranial electrical stimulation;- metallic head implants, cardiac pacemaker or any other device that could malfunction or be displaced by electrical stimulation;- pregnancy or lactation.

Acute migraine treatment will be allowed during the study. Migraine preventive treatments other than CGRP-MAbs must be withdrawn for at least 60 days before inclusion in the trial.

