### Sample Size

The sample size calculation was performed using GPower, version 3.1. According to previous literature (36), a between-groups mean difference of 3 ± 2 migraine days per month was considered significant. The computation was made with the following parameters: confidence interval (two-sided): 95%; power: 80%; ratio of sample size: 1:1; mean change in group 1: −4 days; mean change in group 2: −1 day; standard deviation: 2. The minimum sample size suggested was of 9 patients per group. In consideration of possible dropouts, we set our population size to 30 patients, 15 per group.

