The present trial has a robust double-blind, randomized approach with blinded outcome assessment. The trial complies with the most recent guidelines for neuromodulation in migraine. Besides, the tDCS montage was designed specifically for migraine prevention by reflection on the most plausible neuroanatomical targets. However, the study also has limitations. The study is single-center; besides, its sample will be sufficient to calculate the primary outcome, while subgroup analyses will be only exploratory. We will correct for low numbers by assessing the normality of variable distributions and perform conservative, non-parametric tests for non-normally distributed variables. As an add-on to highly effective migraine preventatives, we cannot exclude that the clinical effect of tDCS in the present RCT will be negative. Nevertheless, we will include patients with a high burden of migraine (≥8 monthly migraine days) to correct for this effect. Besides, a previous trial showed that active tDCS is more effective than sham even on top of topiramate (47), suggesting that tDCS could be an effective add-on migraine preventative. Besides, we will assess not only the possible clinical efficacy of tDCS, but also its effect on brain circuitry; therefore, even results that are clinically neutral will be interesting to discuss with respect to the functional effects of tDCS. Our trial will contribute to assess the possible central, indirect effects of CGRP-MAbs by verifying whether the central circuits of migraine generation can be inhibited in addition to the action of those drugs.

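### The planned active-versus-sham test of change in headache days makes no baseline adjustment, lets the data choose its form, and has unclear priority over within-arm assessment

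*Protocol article*

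**What the plan says.** Efficacy Outcomes defines the endpoint as a change score: "The primary efficacy outcome will be the change in headache days from the 28-day baseline to the 28-day follow-up period". The same section then says: "Each outcome will be assessed in the group of active and sham tDCS; additionally, between-group comparisons will be made".

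Statistical Analysis plans the active-versus-sham comparison of the clinical variables and says it "will be performed using parametric or non-parametric statistics, depending on the data distribution". That section ends: "Outcomes will be compared between the active and sham tDCS groups by chi-squared or t-test statistics as appropriate". The Discussion describes the approach to small numbers as "assessing the normality of variable distributions and perform conservative, non-parametric tests for non-normally distributed variables". None of these places names a covariate or an adjusted model, although every patient keeps a 28-day baseline diary (Baseline section).

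The Sample Size section is built on a between-group difference, with "mean change in group 1: −4 days; mean change in group 2: −1 day", SD 2, two-sided 5% and 80% power. It gives a minimum of 9 per group, raised to 15.

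**The concern.** Three features of the stated plan act together.

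- **No adjustment.** With 15 per arm, the arms can differ at baseline by chance. An arm that starts higher tends to fall more, and an unadjusted change score carries that into the estimate as noise.
- **Test chosen from the data.** A normality check on so few patients tells little. Switching to a rank test also changes what is estimated, so the primary result may no longer be a difference in days.
- **Unclear priority.** Patients enter after "reporting ≥8 monthly migraine days in the last 30 days of observation despite treatment with CGRP-MAbs", and sham has its own expected improvement. Both arms can therefore improve without any effect of stimulation. If within-arm results are reported with p-values beside an additional between-arm test, a reader may take significance in one arm only as evidence of a difference.

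At stake are precision in a trial of 30 patients and a clear statement of which result decides.

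**Working it through.** **Inputs.** From Sample Size: difference 3 days (−4 versus −1), SD of change 2, two-sided 0.05, 15 per arm. That section speaks of migraine days and the primary outcome is headache days, so using SD 2 for headache days is an assumption. The baseline to follow-up correlation ρ is not given and is shown over a range.

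**1. The plan's own figure.** Two-sample t-test (noncentral t), difference 3, SD 2: power is 79.65% at 8 per group and 84.8% at 9. The stated minimum of 9 is reproduced.

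**2. Variance of the two analyses.** With equal baseline and follow-up variance σ²:
- change score: 2σ²(1−ρ)
- ANCOVA residual: σ²(1−ρ²)
- ratio: (1+ρ)/2, i.e. 0.65, 0.75 and 0.85 at ρ = 0.3, 0.5 and 0.7

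Estimating the slope costs an average factor of 1 + 1/(2n−4). At n = 15 this is 1 + 1/26 = 1.038, which gives net ratios of 0.675, 0.779 and 0.883.

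**3. Standard error.** The change score has 2 × √(2/15) = 0.73 day. ANCOVA has 0.73 × √0.779 = 0.64 at ρ = 0.5 and 0.73 × √0.883 = 0.69 at ρ = 0.7. Simulation (10,000 runs per scenario) gave about 0.73, 0.64 and 0.68, and both estimators were within 0.01 day of the truth.

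**4. Chance imbalance.** One day of baseline difference between arms shifts the change-score contrast by 1−ρ, i.e. 0.7, 0.5 or 0.3 day at ρ = 0.3, 0.5 or 0.7. Its share of the change-score variance is (1−ρ)/2 = 0.35, 0.25 or 0.15. ANCOVA takes this share out.

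**5. Power at 15 per arm, SD of change held at 2** (ANCOVA df = 2n−3 = 27):

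| True difference | Change-score t-test | ANCOVA ρ = 0.3 | ρ = 0.5 | ρ = 0.7 | ρ = 0.9 |
|---|---|---|---|---|---|
| 3 days | 97.7% | 99.8% | 99.4% | 98.8% | 97.9% |
| 2 days | 75.3% | 89.5% | 84.9% | 80.2% | 75.7% |

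**6. When ANCOVA loses.** The variances are equal at ρ = 2/1.038 − 1 ≈ 0.93 for 15 per arm. In the limit ρ = 1, power falls from 97.7% to 97.3% (3 days) or from 75.3% to 73.6% (2 days).

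**7. Reading within-arm results as efficacy.** Give both arms the plan's sham change of −1, SD 2. The one-sample noncentrality is (1/2) × √15 = 1.94 on 14 df, and an arm improves significantly with probability 0.438. Then P(active significant, sham not) = 0.438 × (1 − 0.438) = 0.246. For shared changes of 0.5, 1.5 and 2 days the figure is 12.4%, 17.7% and 4.8%, so 25% is close to the worst case.

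**8. Cost of the normality switch.** At 15 per arm with no effect, a Shapiro–Wilk check followed by t-test or Mann–Whitney has simulated type I error of 4.7–5.3%. Taking the smaller of the two p-values gives 5.6–5.9%.

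**The case against.** The strongest reply is that the plan is already sound in principle. Four stronger readings are tempting, and the protocol supports none of them.

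- **That efficacy is judged first within each arm.** No within-arm decision rule is stated. Statistical Analysis names a between-group comparison for the clinical variables, Sample Size is built on a between-group difference, and sham is there to control for placebo and nocebo effects. Only the EEG power analysis is explicitly before versus after by group. What stands is that one sentence leaves the priority unclear.
- **That ANCOVA removes regression to the mean.** Randomisation already balances it between arms on average, and the unadjusted contrast is unbiased. The gain is precision and correction of chance imbalance.
- **That choosing the test from the data inflates false positives.** Under a fixed normality rule it hardly does (step 8). What stands is that no criterion or default test is fixed, which leaves some freedom over the reported result.
- **That the two test statements plainly conflict.** The sentence on chi-squared and t-tests closes the EEG paragraph and may refer to EEG outcomes only.

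It is also fair to say that a condensed article may leave covariates and criteria to a fuller document, and missing detail is not the point here. The article does state an unadjusted, distribution-driven comparison, and a better analysis of data already collected is available. Finally, under the plan's own assumptions power is 97.7%, so adjustment adds at most about 2 points at ρ of 0.3 or more. The benefit is material only if the true effect is smaller than planned or the spread larger.

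**Conclusion.** The point holds as a cheap improvement and a clarification, not as an error of validity. The planned comparison is unbiased but less precise than it could be. For ρ between 0.3 and 0.7, ANCOVA has 0.65 to 0.85 of the variance before the small-sample factor of 1.038. Power for a true 2-day difference rises from about 75% to 80–90%; for the planned 3 days it stays near 98–100%. These figures assume SD of change 2, equal baseline and follow-up variances, and 15 analysed per arm. The value of ρ is an assumption, because the protocol gives none.

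The wording on priority also needs correcting: with an identical 1-day improvement in both arms, significance in active but not sham would appear in about a quarter of trials. That figure measures the risk of a misreading, not of a rule the protocol adopts.

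**What to change.** Before unblinding, amend the analysis text as follows:

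1. State that the active-versus-sham contrast in headache days is the single primary analysis of the primary outcome.
2. Analyse follow-up headache days by ANCOVA on arm and baseline headache days, two-sided 5%, and report the adjusted difference in days with its 95% CI.
3. Replace the normality-driven switch with one named sensitivity analysis, either rank-based ANCOVA or a permutation test of the adjusted difference.
4. Use the same model for the other continuous outcomes, each with its own baseline value.
5. Report within-arm changes descriptively, without p-values.
6. Say whether the closing sentence on chi-squared and t-tests covers the clinical outcomes or only EEG, and align it with item 2.

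The cost is wording and one degree of freedom. No extra patients, visits or measurements are needed. The variance penalty outweighs the gain only if ρ exceeds about 0.93 at 15 per arm, and even then the loss of power is under 2 points for a 2-day difference.

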## Objectives

The primary aim of the present study will be to assess whether tDCS as an add-on treatment to CGRP-MAbs is effective in reducing headache frequency, intensity, and acute medication use in patients with migraine. Secondarily, we will assess the effect of tDCS add-on on migraine-related disability, quality of life, sleep disturbance, and psychological symptoms. To demonstrate and quantify the biological effects of tDCS, we will assess the electroencephalographic (EEG) power changes after tDCS.

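### One primary outcome is named, but the primary aim, the analysis section and the sample-size section do not keep to it

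*Protocol article*

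**What the plan says.** Five places in the protocol bear on what counts as success.

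- **Objectives.** The primary aim is "to assess whether tDCS as an add-on treatment to CGRP-MAbs is effective in reducing headache frequency, intensity, and acute medication use". Disability, quality of life, sleep and psychological symptoms follow as secondary aims, so frequency, intensity and medication use all sit on the primary side. The Abstract gives the same three targets as the aim of the study, without the word primary.
- **Efficacy Outcomes, primary.** "The primary efficacy outcome will be the change in headache days from the 28-day baseline to the 28-day follow-up period".
- **Efficacy Outcomes, others.** "The secondary outcomes will include the change in migraine days, headache hours, mean pain intensity (0–10 Visual Analog Scale), acute treatment consumption (doses"), followed by the questionnaire scores. The section adds: "The change in the number of days with low, medium, and high disability will also be assessed". On contrasts it says: "Each outcome will be assessed in the group of active and sham tDCS; additionally, between-group comparisons will be made".
- **Statistical Analysis.** "Primary analyses will be performed on primary and secondary outcomes". The next sentence sets these against subgroup analyses, the only ones it labels exploratory.
- **Sample Size.** The calculation is for a between-group difference of 3 migraine days per month with SD 2, in one two-sided comparison at the 95% level with 80% power. It gives 9 per group, raised to 15 for dropouts.

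**The concern.** A trial that names one primary outcome controls its error rate only if its efficacy conclusion rests on that outcome. Here, two of the three components of the primary aim are secondary outcomes, and the analysis section gives primary and secondary outcomes the same analysis label. The document does not say which statement prevails.

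The practical risk comes at reporting. Suppose headache days show no difference but pain intensity or acute doses reach p<0.05. The authors could point to the Objectives section and say the primary aim was met, and to the Statistical Analysis section to call the result a primary analysis. Both statements would match the published protocol. The sample-size section adds to the blur, because the endpoint it justifies is not the one named as primary.

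**Working it through.** **1. The plan's own sample size.**

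Inputs (Sample Size section): mean changes −4 and −1 days, so the difference is −1 − (−4) = 3 days; SD 2; two-sided 5%; power 80%; 1:1 allocation. The standardised difference is d = 3/2 = 1.5.

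For a two-sample t-test, the noncentrality is d × √(n/2) with 2n − 2 degrees of freedom:

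- n = 8 per group: 1.5 × √4 = 3.00, power 79.65%
- n = 9 per group: 1.5 × √4.5 = 3.18, power 84.8%
- n = 15 per group: 1.5 × √7.5 = 4.11, power 97.7%

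The stated 9 per group is reproduced. It is the right number for one test, on migraine days, at two-sided 5%. It makes no allowance for more than one route to success, and the section gives no difference or SD for headache days.

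**2. The designations side by side.**

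| Target | Objectives | Efficacy Outcomes | Statistical Analysis | Sample Size |
|---|---|---|---|---|
| Headache days | primary aim (as frequency) | primary | primary analysis | not used |
| Pain intensity | primary aim | secondary | primary analysis | not used |
| Acute medication doses | primary aim | secondary | primary analysis | not used |
| Migraine days | could also fall under frequency | secondary | primary analysis | basis of the calculation |

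Only the Efficacy Outcomes section separates headache days from the rest.

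**3. What the literal reading of the aim would cost.**

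Assumptions, none stated in the protocol: one between-arm test for each of the three targets, each at two-sided 5%, no true effect on any, and any one significant result taken as success.

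- Independent tests: 1 − (1 − 0.05)³ = 1 − 0.857 = 14.3%.
- Correlated tests, from 200,000 simulated sets of three equally correlated standard normal statistics, counting sets with any |z| > 1.96: 12.6% at correlation 0.5, 11.0% at 0.7 and 8.4% at 0.9.
- Headache days alone, between arms: 5%.

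The protocol gives no correlations between outcomes, so a range is shown. Every value in it exceeds 5%.

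**The case against.** The strongest reply is that the primary outcome is already fixed. The Efficacy Outcomes section names it, gives its time window and defines a headache day, and the Discussion speaks of the primary outcome in the singular. If success rests on the between-arm test of that outcome at 5%, the error rate is 5%. The Objectives section lists broad domains, not defined endpoints. The sentence in the Statistical Analysis section keeps the labels primary and secondary for the outcomes, and may use primary analyses only to mean the whole-sample analyses as opposed to the subgroups.

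Much of this stands. A reader might infer that the trial has no fixed success criterion, or that a significant result on any of its many outcomes would count. The documents do not support that. No passage states such a rule, and none sets a 5% level for each secondary test: the Statistical Analysis section mentions only 95% confidence limits, and the two-sided 95% in the Sample Size section belongs to that calculation. Nor is the absence of an adjustment across secondary outcomes a fault here, because it may be in an analysis plan that is not shown. A false-positive rate computed over the full list of outcomes would therefore describe a rule the protocol does not contain. A joint power for success on all three targets cannot be established either, because no effect size is given for intensity or doses.

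The reply does not remove the mismatch between aim and outcomes. Reading primary analyses as not subgroup is plausible but unstated, and it leaves the Objectives section in conflict with the Efficacy Outcomes section. It also leaves the sample size on a secondary outcome.

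**Conclusion.** The concern holds as an inconsistency in the text. One primary outcome is designated; the primary aim, the analysis sentence and the sample-size endpoint do not respect it. The consequence is a literal route to reporting the primary aim as met on intensity or acute doses without an effect on headache days. Under the assumptions in the working, that route carries a false-positive chance of about 14% with independent tests and about 8% to 13% at correlations of 0.9 to 0.5, against 5% for the named outcome alone.

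The sample-size arithmetic is correct for what it states; the issue there is only the endpoint. This should be fixed, preferably before unblinding so that the clarification is credible, but it does not undermine the design.

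**What to change.** - **Objectives:** limit the primary aim to the reduction in headache days, and move intensity and acute medication use to the secondary aims. Align the general aim in the Abstract.
- **Statistical Analysis:** replace the sentence on primary analyses with text to this effect: the between-arm comparison of change in headache days, at two-sided 5%, is the sole confirmatory test, and efficacy is concluded from it alone; secondary outcomes are supportive and reported as estimates with 95% confidence intervals. Naming the between-arm contrast also settles the status of the within-arm assessments.
- **Sample Size:** reconcile the endpoint with the primary outcome, either by justifying a difference and SD for headache days or by stating that the migraine-day figures are carried over as an assumption.

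A gatekeeping step with Holm adjustment across the secondary outcomes is optional, needed only if confirmatory secondary claims are wanted.

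The cost is wording, plus a short justification for the sample-size inputs; the first two changes need no extra patients or data. The downside is that an isolated significant secondary result could no longer be presented as proof of efficacy.

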### EEG Recording

Patients will perform a 10-min resting EEG recording (5 min eyes-open, 5-min eyes-closed), immediately before the first and immediately after the last tDCS session. EEG will be performed with a 64-channel apparel (BrainAmp, Brain Products GmbH) according to the 10–10 international system.

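### The electrode-level EEG analysis is worded as uncorrected before-after tests within each arm, and the plan does not make the active-versus-sham contrast the basis for the EEG conclusion

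*Protocol article*

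**What the plan says.** The Objectives section gives the purpose of the EEG: "To demonstrate and quantify the biological effects of tDCS". Under EEG Recording, "EEG will be performed with a 64-channel apparel", with five minutes eyes open and five minutes eyes closed, taken "immediately before the first and immediately after the last tDCS session". Efficacy Outcomes calls the EEG the additional outcome and defines it as change in spectral power and coherence in "delta (1–4 Hz), theta (5–7 Hz), alpha (8–12 Hz), and beta bands (13–30 Hz), both overall and over the occipital regions".

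The electrode-level test is in Statistical Analysis. For each arm separately, "the power change before vs. after tDCS will be compared for each electrode and each frequency band". Occipital alpha power is to receive particular attention, but it is not declared as a single test. The section continues: "The EEG index changes will be correlated with changes in migraine parameters", and lists headache days, migraine days, pain intensity, acute medication and questionnaire scores. Source localisation follows for those EEG indexes considered relevant.

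Two sentences provide for a comparison between arms. Efficacy Outcomes says that each outcome is assessed in each group and that group comparisons are made in addition. The EEG paragraph of Statistical Analysis ends with a general statement that outcomes are compared between active and sham by chi-squared or t-test. The list of variables for group comparison earlier in that section names clinical measures and questionnaires, not EEG.

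**The concern.** A sham arm is there so that change after active stimulation can be set against change without it. A before-after test inside one arm also picks up time, vigilance and migraine phase. The Introduction itself says that cortical responsivity shifts over the migraine cycle, while the recordings are timed only by stimulation session. Finding electrodes that are significant in the active arm and not in the sham arm is not a test of the difference between arms.

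The number of tests makes this worse. Hundreds of electrode-by-band tests per arm, plus correlations with many outcomes, will usually produce some nominally significant results even if stimulation does nothing.

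The article means to rely on these results. The Objectives speak of demonstrating biological effects. Statistical Analysis intends the correlations to tie brain changes directly to migraine severity. The Discussion plans to interpret the functional effects even if the clinical result is neutral. Subgroup analyses are labelled exploratory, but the EEG tests and correlations are not.

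**Working it through.** **Plan's own figure.** The article gives no error rate or sample size for the EEG tests. Its only calculation is for the clinical endpoint: difference 3 days, SD 2, two-sided 5%, power 80%, result 9 per group. The exact noncentral t gives 79.7% power at 8 per group and 84.8% at 9, so 9 is reproduced. It says nothing about the EEG.

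**Inputs.** 64 channels and two eye conditions (EEG Recording); 4 bands, overall and occipital (Efficacy Outcomes); 15 patients per arm (Sample Size). The two-sided 5% level is stated for the sample size and assumed here for the EEG.

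**Number of tests and expected false positives under the null**

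- One arm: 64 × 4 = 256; 256 × 0.05 = 12.8.
- Both arms: 512; 512 × 0.05 = 25.6.
- Both arms, eye conditions analysed separately (the text does not say): 1,024; 1,024 × 0.05 = 51.2.

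These expected counts do not depend on how strongly electrodes are correlated. Coherence is not counted.

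**Chance of at least one false positive.** Under independence, one arm gives 1 − 0.95^256 = 0.999998. Scalp electrodes are correlated, so this was also simulated: 2,000 runs, 15 per arm, no true change, equal correlation among electrodes, bands independent. The correlations are assumptions. Correlation between bands would lower the probabilities further.

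| Electrode correlation | Within one arm (256 tests) | In either arm (512 tests) | Active versus sham (256 tests) |
|---|---|---|---|
| 0.5 | 0.99 | 1.00 | 0.99 |
| 0.7 | 0.93 | 1.00 | 0.91 |
| 0.9 | 0.62 | 0.86 | 0.60 |
| 0.95 | 0.49 | 0.73 | 0.47 |

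The last column shows that changing to the between-arm contrast, still uncorrected, leaves the multiplicity almost as it was. For comparison, one prespecified test has a 5% error rate. The regional set of 4 bands × 2 regions = 8 tests has 8 × 0.05 = 0.4 expected false positives and at most 1 − 0.95^8 = 0.34 chance of any under independence. A Bonferroni level for 256 tests is 0.05 / 256 = 0.000195.

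**Reading the two arms separately.** Suppose both arms truly change by the same d (in SD units of change). With p the power of a one-sample t-test at n = 15 (14 df, noncentrality d√15), the chance that exactly one arm is significant is 2p(1 − p).

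- d = 0.3: p = 0.192, giving 0.31.
- d = 0.5: p = 0.438, giving 0.49.
- d = 0.53: p = 0.481, giving 0.50.
- d = 0.75: p = 0.771, giving 0.35.

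So 31% to 50% of such cases would look like a difference between arms when there is none.

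**Correlations.** The article names five parameters or groups of parameters. Counting the five questionnaires singly gives 4 + 5 = 9; 13 is an assumed upper figure.

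- 256 EEG indexes: 256 × 5 = 1,280 to 256 × 13 = 3,328 coefficients, with 64 to 166 expected false positives.
- 8 regional indexes only: 40 to 104 coefficients, with 2 to about 5 expected.

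The |r| needed for p < 0.05 is about 0.51 within one arm (n = 15) and about 0.36 pooled (n = 30). The article does not say which is meant. Coefficients that pass such thresholds in small samples tend to be exaggerated.

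**The case against.** The strongest reply is that the active-versus-sham comparison is planned. Efficacy Outcomes promises group comparisons directly after defining the EEG outcome, and the EEG paragraph of Statistical Analysis closes with one. A t-test on change scores is the right kind of contrast, and it deals with influences shared by both arms. Migraine phase is balanced in expectation by randomisation, so it adds noise to that contrast and not bias. A reader might infer from the within-arm wording that the trial cannot show an effect of active stimulation; the text does not support that. What remains is that the general sentences do not say that this contrast settles the EEG question, or whether it applies by electrode, by region or overall.

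Second, the electrode-level correction may stand in an analysis plan or full protocol that is not shown, and an article commonly leaves it there. That is fair, and the missing correction is not the finding by itself. The finding is the within-arm test that the article states, together with its confirmatory language.

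Third, the EEG is an additional outcome with an occipital alpha focus, and no efficacy claim or sample size rests on the map. This limits the weight of the point. It does not remove it, because the Objectives and Discussion intend to draw conclusions from the EEG in its own right.

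**Conclusion.** The point holds as a fault in how a stated analysis is set up. As worded, the electrode-by-band analysis consists of separate within-arm tests, which do not establish an effect of active stimulation. Uncorrected, they carry about 13 expected false positives per arm under the null. At least one in either arm is very likely: 0.73 to 1.00 over assumed electrode correlations of 0.95 down to 0.5, with bands taken as independent.

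Two further readings go too far. False positives are not guaranteed: with highly correlated electrodes (0.9 to 0.95) the chance of any in a single arm is 0.49 to 0.62. A correlation pooled over arms would not reflect only the arm difference; it mixes between-arm and within-arm association, which is why adjustment for arm is needed.

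The consequence is confined to the EEG conclusions. The primary headache-day endpoint is not affected.

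**What to change.** 1. Name one key EEG test: change in occipital alpha power in one stated eye condition, active versus sham, by ANCOVA with the pre-stimulation value as covariate. The protocol already singles out this band and region. A t-test on change would address the same contrast; ANCOVA is preferred because it also adjusts for chance imbalance in the pre-stimulation EEG.
2. Analyse the electrode-by-band map as the active-versus-sham difference in change, with error control such as a cluster-based permutation test. Report within-arm before-after results as descriptive only.
3. Keep one key correlation, occipital alpha change with headache-day change, adjusted for arm. Label all other correlations exploratory.
4. Do not adjust for headache status on the day of the post-stimulation recording. It is measured after treatment, and adjusting could remove or bias part of the effect. Use the diary at most to describe it.

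The cost is a change of analysis wording and a standard permutation routine, with no new patients or recordings. The downside is fewer nominally significant electrodes to report.
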